# Managing Cognitive Decline Through a Social Robot–Based Intervention: Protocol for the engAGE Proof of Concept and Randomized Controlled Trial

**DOI:** 10.2196/67601

**Published:** 2025-09-02

**Keywords:** older people, older adults, mild cognitive impairment, social robotics, technology for elderly, digital health, cognitive training, innovation in health care

## Abstract

**Background:**

Dementia is challenging society in terms of the quality of life, the costs of health care systems, and caregivers’ burden. Dementia is often preceded by a status of mild cognitive impairment (MCI), during which a healthy lifestyle and cognitive therapy seem to be effective in counteracting the decline.

**Objective:**

The engAGE (Managing Cognitive Decline Through Theatre Therapy, Artificial Intelligence, and Social Robot–Driven Interventions) project aimed to build a technological platform to counteract cognitive decline in older adults with MCI through both cognitive therapy and lifestyle management.

**Methods:**

The engAGE platform was built around the social robot Pepper, which provides cognitive therapy. An activity tracker and a mobile app were also integrated within the platform to help older adults with MCI monitor their sleep and physical activity, in addition to offering cognitive games at home. The proof of concept (PoC) of engAGE was designed as a 6-month long randomized controlled trial (RCT) aimed to test the solution in three European countries: Italy, Switzerland, and Norway. During this period, under the supervision of a psychologist or a therapist, Pepper provided cognitive therapy on a weekly basis at health care or daycare facilities. In parallel, the use of the mobile app and the activity tracker was recommended on a daily basis. Participants were recruited through health care institutions and care organizations and evaluated through face-to-face interviews. The primary interest of the study was to assess the impact of engAGE on cognitive capacity through the Montreal Cognitive Assessment (MoCA) and the Memory Assessment Clinic Questionnaire (MAC-Q). In addition, changes in social engagement and quality of life were measured through the University of California, Los Angeles (UCLA) Loneliness Scale and the Warwick-Edinburgh Mental Well-Being Scale (WEMWBS). The PoC also focused on the acceptability and usability of engAGE, evaluated through the System Usability Scale (SUS) and the Unified Theory of Acceptance and Use of Technology (UTAUT) questionnaire. In addition, data were collected regarding the frequency of weekly sessions and access to the mobile app, as well as activity tracker measurements.

**Results:**

Data collection commenced in November 2023 and finished in July 2024, with the enrollment of 49 older adults with MCI (n=40, 81.6%, assigned to the experimental group [EG] and n=9, 18.4%, to the control group [CG]) conducted from October 2023 to April 2024. Data analysis was concluded in November 2024, and results will be published by 2026.

**Conclusions:**

The engAGE PoC represents an innovative study focused on the impact of a technology-based multidomain intervention designed for older adults with MCI that aimed to counteract cognitive decline through cognitive training, as well as improvement in terms of the quality of life, social engagement, physical activity, and sleep quality of primary end users.

**Trial Registration:**

ClinicalTrials.gov NCT06302686; https://clinicaltrials.gov/study/NCT06302686

**International Registered Report Identifier (IRRID):**

RR1-10.2196/67601

## Introduction

### Background

Dementia is a chronic neurodegenerative syndrome characterized by deficits in cognitive functions, associated with the loss of daily function and with mental and behavioral disorders. There are over 1 million people with dementia in Italy, of which 54% have Alzheimer’s disease and about 16% have vascular dementia [1]. The Swiss Federal Office of Public Health expects an increase in the number of people diagnosed with dementia to over 190,000 individuals by 2030 and to almost 300,000 by 2060 [2]. The same trend is expected in Norway, where the number of people with dementia is estimated to more than double from 2020 to 2050 [3]. According to the literature, cognitive interventions [4], regular physical activity [5,6], and reminiscence therapy appear to be effective in the treatment of people with mild-to-moderate dementia. Cognitive stimulation programs, computerized individual cognitive training, and physical exercise appear to be able to induce a significant improvement in cognitive performance, quality of life, and well-being in people with mild-to-moderate dementia [7-9]. Several studies show that, especially in the early stages of the disease, stimulation and participation in various types of activities can help counterbalance the cognitive changes related to the pathology, thanks to cognitive plasticity [10,11]. Neurocognitive disorders, in particular dementia, represent a major challenge for society. Efforts to reduce the burden for caregivers, as well as for society at large, are imperative. Older adults generally report higher preferences for their home over other living arrangements, and from the societal point of view this can contribute to the burden of care, for example, for their families. Dementia caregivers are at high risk of care burden, anxiety, and stress, which exposes them to a higher rate of mortality compared to noncaregivers [12]. Thus, promoting aging in place for people with dementia should not constitute a strategy to shift the burden of care from formal care services to informal caregivers. Instead, efforts should focus on reducing caregiver stress. Part of the difficulties and stress related to caregiving might be prevented by new information and communication technologies (ICT) and by developing innovative support services for these people. The introduction of innovative and cost-effective interventions to reduce the burden of dementia on public finances and individual families should be envisaged. Several digital interventions have been developed to address the needs of individuals with mild cognitive impairment (MCI), targeting cognitive stimulation, social engagement, and caregiver support. These include cognitive training apps [13,14], telehealth platforms [15,16], and social robot–based interventions [17,18]. Despite the growing availability of digital solutions, a significant gap remains in providing efficient, integrated, personalized, and adaptive home-based care for individuals with MCI. In fact, existing solutions often focus on single domains, rely on single technologies, and lack the ability to seamlessly integrate various components to address the complex needs of older adults with MCI.

### The engAGE Project

In this scenario, the engAGE (Managing Cognitive Decline Through Theatre Therapy, Artificial Intelligence, and Social Robot**–**Driven Interventions) project, cofinanced by the Ambient and Assisted Living (AAL) program of the European Union [19], aimed to counteract and slow down cognitive decline progression, enhance the intrinsic capacity of the users, and support the well-being of older adults with MCI by providing an ecosystem of services based on an innovative system that integrates social robots, mobile apps, and wearable sensors. Moreover, the engAGE project combined home-based intervention (daily usage of a mobile app and a wearable fitness tracker) with group cognitive training at a health care facility (weekly social robot–driven sessions). Thus, engAGE targeted the following challenges and needs for older adults with MCI, informal caregivers (family members), and formal caregivers (health care professionals):

The project was primarily focused on older adults with MCI, aiming to improve their quality of life and well-being, allowing them to preserve their identity and reduce stress, memory loss, or communication challenges. The social robot can be a great tool in engaging older adults in these kinds of activities. It is always available and can provide verbal clues or suggestions according to each older adult’s wishes, needs, and memories. Moreover, the social robot may coach older adults to perform daily activities with greater independence (ie, coaching stepwise, prompting to complete activities at home).The project provides support to caregivers as well. Since caring for people with MCI puts a significant burden on informal caregivers, having the support of a technological platform can reduce anxiety, worry, and stress. Caregivers can personalize the content of the interventions to the wishes and preferences of older adults.

### Goal of the Study

This paper presents the study protocol of the engAGE proof of concept (PoC). The study aimed to demonstrate the viability of integrating social robot–based cognitive therapy in a health care facility with a mobile app and an activity tracker for daily use at home for counteracting cognitive decline in older adults with MCI. To provide more robust results in this sense, the study was designed as a 6-month long randomized controlled trial (RCT) in a real scenario in three European countries: Italy, Norway, and Switzerland. The study primarily evaluated cognitive capacity changes in older adults with MCI, in addition to assessing the impact on the quality of life and social dimension of primary end users, as well as the acceptability and usability of the engAGE platform. Moreover, the reduction in the stress and care load of formal and informal caregivers was measured. All measurements were performed at the beginning and end of the study to analyze intra- and intergroup differences. The novelty of this study design is the combination of at-home and in-place interventions to maximize the impact of cognitive stimulation through technology, minimizing the caregivers’ burden and encouraging the social connectedness among end users with the care network. The paper provides an up-to-date methodology of an interventional study to those researchers, scientists, and stakeholders who are interested in the use of social robots and ICT in health care and digital health. Finally, the paper discusses in depth the ethical issues concerning the adoption of social robots, machine learning (ML) algorithms, and health data management, along with the long-debated question of the informed consent form signed by people with MCI.

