#### Formal Caregivers

Care professionals or formal caregivers are professionally responsible for dementia care. They are trusted agents for people with MCI and have direct contact with older adults and provide care when needed.

Formal caregivers are case managers, neurologists, psychotherapists, occupational therapists, and nurses. The case manager was responsible for the organization. The neurologist was a specialized medical doctor who diagnosed the disease and prescribed treatment. The psychotherapist led the intervention, whereas the nurses and occupation therapists acted as assistants. These professionals might be especially found in daycare, but they are available in residential home care as well (Textbox 4).

Inclusion and exclusion criteria for formal caregivers.

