### Outcomes

The PoC aimed to assess the feasibility of using the engAGE platform as a support tool to counteract cognitive decline in older adults with MCI. For this reason, the primary interest was to assess the impact of the engAGE platform on cognitive capacity. Secondarily, the study also focused on the impact on the social dimension and quality of life, as well as the usability and acceptability of the platform. All the outcomes are presented in Table 1.

**Table 1 table1:** Tools and dimensions of the primary end users’ protocol.

Outcome	Clinical assessment
Perceived stability of cognitive status by older adults	MAC-Q^a^ [26]
Acceptability of the engAGE^b^ platform	UTAUT^c^ [29]
Social connectedness of older adults	UCLA^d^ [30]
Reduction in the caregiver burden of formal and informal carers	Zarit et al [31]
Adherence to intervention	Ad hoc questionnaire
Well-being of informal caregivers	WEMWBS^e^ [32]
Quality of life of older adults	EuroQol 5-Dimension 5-Level (EQ-5D-5L) [33], Quality of Life-Alzheimer’s Disease (QoL-AD) scale [34]
Usability and affordability of the solution of informal caregiver	SUS^f^ [35]
Improving the quality of work of formal carers	Ad hoc questionnaire

^a^MAC-Q: Memory Assessment Clinic Questionnaire.

^b^engAGE: Managing Cognitive Decline Through Theatre Therapy, Artificial Intelligence, and Social Robot–Driven Interventions.

^c^UTAUT: Unified Theory of Acceptance and Use of Technology.

^d^UCLA: University of California, Los Angeles.

^e^WEMWBS: Warwick-Edinburgh Mental Well-Being Scale.

^f^SUS: System Usability Scale.

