Outcomes that concern efficacy of the engAGE intervention were considered exploratory and dealt with the metrics about cognitive capacity, quality of life, social dimension, and stress and care load relief (for caregivers). In particular, to explore the potential efficacy, changes in these domains before and after the intervention were analyzed. Paired *t* tests (for normally distributed data) or Wilcoxon signed-rank tests (for nonnormally distributed data) were used to compare pre- and postintervention scores within each group, while independent samples *t* tests or Mann-Whitney U tests were performed to assess between-group differences in change scores. Moreover, effect sizes (Cohen d or Cliff δ) were calculated to quantify the magnitude of any observed differences. Due to the nature of the PoC, this study was not powered to detect statistical significance. *P* values will be reported without adjustments for multiple comparisons and interpreted with caution. All analyses were planned for descriptive purposes, and only participants with at least 80% of adherence to the intervention were considered for analysis.

The aforementioned analyses were also applied to acceptance and usability measurements (ie, UTAUT and SUS scores) that provided insights into the primary goal of the study: the feasibility of the intervention. Data from the ML service were analyzed to correlate physical activity, sleep parameters, game scores, and self-assessment data. Longitudinal data analysis techniques (eg, mixed effects models) were used to analyze changes in these parameters over time and assess potential correlations with cognitive and quality-of-life outcomes.

The first step in the data analysis dealt with the description of the sample. Continuous variables will be reported as either the mean (SD) or the median (IQR) on the basis of their distribution (assessed using the Kolmogorov-Smirnov test). Categorical variables will be expressed as an absolute number and percentage. Mann-Whitney U tests (for nonnormal distribution) or chi-square tests (for normal or nonnormal distribution) were used to compare independent and dependent variables between the pre- and postintervention conditions, in addition to simple descriptive statistics (means, medians, and SDs, as appropriate).

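### Caregiver burden is to be compared between arms for formal and informal carers alike, but no valid between-arm contrast is defined for formal carers, some of whom deliver the experimental sessions

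*Protocol article*

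**What the plan says.** Goal of the Study states that "the reduction in the stress and care load of formal and informal caregivers was measured". The next sentence reads "All measurements were performed at the beginning and end of the study to analyze intra- and intergroup differences". Table 1 under Outcomes has one burden row for both kinds of carer, "Reduction in the caregiver burden of formal and informal carers", with one scale, and a separate row for staff, "Improving the quality of work of formal carers", measured by an ad hoc questionnaire.

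Data Analysis counts "stress and care load relief (for caregivers" among the exploratory efficacy domains. For those domains it prescribes paired tests "to compare pre- and postintervention scores within each group", and independent-samples tests that "were performed to assess between-group differences in change scores".

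On the role of formal carers, the Formal Caregivers section says "The psychotherapist led the intervention, whereas the nurses and occupation therapists acted as assistants". The Experimental Group section adds that formal caregivers supervise the robot interaction and assign participants' activities. The Control Group section describes a booklet, with no contact during the trial unless the participant wants it.

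**The concern.** A between-arm test of change needs each measured person to belong to one arm, and the arms to differ only by allocation and what follows from it. An informal caregiver can meet this by following the randomised relative. A therapist or nurse who runs the robot sessions cannot, because that job exists only in the experimental arm, and the same person may also look after control participants at the same centre.

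Without a control counterpart, a change in staff scores over 6 months may reflect staffing, season or growing familiarity with the robot as much as the platform. The raters also deliver the service and take on its weekly session of about 1 hour. If such a change is reported beside the informal-carer result under one burden heading in a trial labelled randomised, it may be read as a randomised effect. Results says that lower caregiver load and stress will help determine how important the platform is, and the Discussion summary expects less caregiver burden.

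**Working it through.** No power or sample size figure bears on this point, so the check sets the sections side by side.

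1. **Is formal-carer burden an outcome?** Yes. Goal of the Study and Table 1 both name formal carers.
2. **Is it compared between arms?** Yes for burden. Data Analysis lists caregiver load among the domains given independent-samples tests, and Table 1 defines burden for formal and informal carers. For work quality the support is thinner: it is absent from the Data Analysis list, so its between-arm test rests only on the sentence in Goal of the Study about all measurements.
3. **Who is randomised?** Older adults only (Recruitment). The planned numbers confirm it: 20 + 20 + 10 = 50 experimental and 10 + 10 + 10 = 30 control over Italy, Switzerland and Norway. These add to the 80 given in Study Design, all of them primary end users. No count of formal carers appears, in total or by arm.
4. **Are formal carers placed in an arm by any other rule?** No section does so.
5. **Where do the described staff sit?** Occupational therapists, psychologists and psychotherapists supervise the sessions (The Experimental Group). The psychotherapist leads, and nurses and occupational therapists assist (Formal Caregivers). The control condition has no sessions, hence no session staff.
6. **Could any formal carer follow a participant's arm?** Possibly. Textbox 2 lets a participant of either arm qualify with an informal or a formal caregiver, and Textbox 4 admits professionals paid by participants. Case managers and neurologists are also named and are not said to run sessions. The article sets up no analysis that uses these links.

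For session staff, steps 3 to 5 leave the independent-samples test without a control group. The paired test can still be computed, but it yields an uncontrolled change.

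**The case against.** The strongest reply is that the gap is one of definition. Every participant, control participants included, needs an informal or formal caregiver, so some formal carers could be classified by their client's arm. The linking rule may stand in a full protocol or analysis plan that is not shown. The sentence about all measurements also cannot be literal, since platform acceptability and usability mean little for a control group given a booklet. Finally, the efficacy analyses are declared exploratory, unpowered and descriptive.

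Part of this stands. A reader might infer that no between-arm contrast could exist for any formal carer. The documents do not support that, because of the exception in step 6. A reader might also infer that formal and informal scores are pooled, or that one carer's score is attached to several participants so that standard errors come out too small. The article plans neither. A shared row in Table 1 names an outcome and a scale, not an analysis set, and eligibility is kept separate for the two kinds of carer. That the same staff serve both arms is a possibility, not a documented fact. Nor is lack of randomisation the defect in itself, since informal caregivers are not randomised either.

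The reply does not remove the core. The article states the comparison and the tests itself, and its design does not supply a control side for the staff it describes. Calling the analysis exploratory does not turn an uncontrolled change into a randomised one.

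**Conclusion.** The point holds for formal carers who lead, assist or supervise the sessions: no valid between-arm contrast is defined for them, and their before-after change is uncontrolled. It holds firmly for burden and more weakly for work quality, where the between-arm test rests on one sentence in Goal of the Study. It may not hold for a formal carer tied to one participant.

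The size cannot be given in figures, because neither the number of formal carers nor their links to participants is stated. The cognitive and other participant-level results are unaffected. What is at stake is one supplementary claim, that the platform relieves formal carers, and the clarity of the informal-carer result beside it. The conclusion assumes that the article describes the staff roles as they were carried out. It is worth correcting before the results are published.

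**What to change.** - **Between-arm comparison.** Limit the caregiver-burden comparison in Data Analysis to informal caregivers, analysed in the arm of the older adult they care for, where such a caregiver exists. Textbox 2 allows a participant to have only a formal caregiver, so the number of older adults with an informal caregiver should be given for each arm.
- **Formal carers.** Report burden and work quality separately from informal carers, once per person, as an uncontrolled descriptive before-after series. Make no between-arm test and no claim that a reduction is attributable to the platform.
- **Wording.** Reword Goal of the Study, the two Table 1 rows that name formal carers, and the Results sentence on caregiver load so that they describe staff experience and no longer presuppose a benefit to staff.

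The cost is wording and a limited re-analysis of data already collected. The downside is that the formal-carer benefit claim becomes descriptive only.

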## Methods

### The engAGE Platform

The engAGE system offers 4 main services built around a social robot for self-managing and sustaining the cognitive function of older adults with MCI [20]: (1) holistic monitoring of daily life activities and perceived health state and well-being; (2) assessment of cognitive state and potential decline by leveraging ML algorithms; (3) social robot–based cognitive function support and coaching using cognitive games and storytelling scenarios; and (4) communication, cognitive stimulation, and personalization platform for end users. Figure 1 schematizes the engAGE platform services with the integration of social robots, sensor-based monitoring, and ML techniques. The primary end users (older adults) mainly interact with three devices: the social robot Pepper, a tablet, and a wearable fitness tracker (Fitbit). Formal caregivers supervise the execution of end users’ activities and help them, when needed. The interaction is through the device’s associated dashboards.

